### Secondary outcome measures

#### Parenting confidence

Parenting confidence is assessed with the Karitane Parenting Confidence Scale (KPCS, [49]). The KPCS consists of 15 items. An example item is: ‘I know what to do when my baby cries’. All items are rated on a four-point scale (0 = ’No, hardly ever’, 1 = ’No, not very often’, 2 = ’Yes, some of the time’, 3 = ’Yes, most of the time’). One item is negatively stated and therefore reverse coded. Two items can be marked as ‘Not applicable’, in that case these items are scored as a ‘2’. All items can be summed to generate a total score, which can range from 0 to 45. Higher scores indicate a higher level of parenting confidence.

#### Parental concerns with regard to the infant

Parental concerns regarding crying, nutrition and sleep behavior of the infant are assessed using three five-point Likert scales. An example item is ‘I worry about the crying of my baby’. Answer options range from ‘Strongly agree’ to ‘Strongly disagree’. On another five-point Likert scale, parents can rate if they worry about other things concerning the baby (‘Strongly agree’ to ‘Strongly disagree’), followed by an open text field where they can list things concerning the baby where they worry about.

#### Background variables

In order to control for possible group differences and to aid a correct interpretation of the results, we assess a variety of relevant background variables and possible confounders. Characteristics that are assessed with regard to the responding parent and the family include: date of birth, gender, country of birth of the responding parent and his/her parents, educational level, relationship status, living situation (living with/without partner), health, sleep, anxiety and depressive symptoms (Hospital Anxiety and Depression Scale HADS [50, 51], employment status and working hours. Child (related) characteristics that are assessed include: parity, single or multiple birth, gestational age, gender, birth weight and health. Finally, other measurements that are assessed include infant carrying, experience with infant massage, (breast)feeding, use of childcare, the occurrence of stressful life events during the study period and received support from- and satisfaction with the PCH.

#### Process variables

The process evaluation questionnaire at T1 (parents in the intervention group only) includes questions concerning frequency, duration, content of and satisfaction with the infant massage intervention. The semi-structured logbooks the intervening professionals (nurses) complete after each intervention session, consist of pre-structured registration booklets. Amongst other things, the nurses are asked to indicate to what extent the goals of the session have been achieved, if they deviated from the standard procedure and if so, why and in what way, and whether the contact and cooperation with the parents was pleasant. Finally, interviews are conducted with five to ten parents who participated in the intervention and 4–6 professionals, focused on their experiences with the intervention, recommendations, and preconditions for (further) implementation.

## Data management

All data will be handled strictly confidentially and in accordance with the guidelines of the EU General Data Protection Regulation. All procedures with regard to handling of the data are described in a Data Management Plan, which is submitted to the grant provider ZonMw.

Data used for analyses is pseudonymized after data collection, by giving each respondent a respondent number. The list of names with respondent numbers is kept separately from the research data. All digital data is stored in a secured vault at (TNO) SharePoint Online, with access restricted for project members only. The data is located within the European Union (Ireland and the Netherlands). Access to the information is only possible through Multi Factor Authentication. TNO makes a daily back-up of the information. Both for SharePoint Online and for the backup use is made of encryption 'in transit' and 'at rest’. Paper questionnaires are marked with the respondent number. After completion, the papers are scanned and subsequently destroyed. The answers are entered into the digital datasets. Both the scanned questionnaires and the datasets are stored in the secured vault at (TNO) SharePoint Online as described above. Collected hair samples are marked with the respondent number, and are securely stored in areas with limited access, both at the PCH locations and at TNO until the samples are sent away to the lab (Dresden LabService GmbH) to be analyzed and subsequently discarded.

## Statistical analysis

All data is to be handled according to standard procedures. Demographic characteristics and study outcomes will be described for each group, using means and standard deviations for continuous outcomes and proportions for categorical data. The comparability of the groups at baseline (T0) will be explored. Differences will be taken into account during further analyses. The pattern of missingness will be checked before the analyses. All measures will be controlled for outliers and checked for normality. Skewed continuous outcomes will be transformed. The level of significance (*p*-value) is set at *p* < 0.05 in all analyses.

Primary and secondary outcomes will be compared between the intervention and control groups using *T*-tests and (multilevel and multivariate) analyses of (co)variance. Differences between the intervention group and the control group at T1 and at T2 will be assessed, while correcting for the baseline measures (T0). Additionally, we will correct for possible differences between the groups by adding covariates or by applying propensity score weighting [40]. In the latter method, participants are taken more or less into account in a comparison between intervention and control groups based on covariates. Furthermore, we will investigate the influence of possible moderating factors, such as depressive symptoms of the parent and premature birth.

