### Participants

#### Sample size calculation

As effect sizes as found in previous research were heterogenous (see Introduction), a medium effect size (Cohen’s *d* = 0.50) was included as the basis for the power and sample size calculation. Based on an ANOVA analysis between two groups of equal size with a Cohen’s *d* effect size of 0.50, 84 participants per research arm are required for a power of 0.9. However, because it is not possible to randomly assign participants or clusters, it is necessary to correct for possible differences between the groups e.g. by adding covariates or applying propensity score weighting [40]. An effective sample size reduction of 20% is taken into account, resulting in required minimum of 105 participants per arm to retain power. In addition, we account for a non-response of 30% due to missing data and/or dropout from the study. Consequently, we aim to recruit a total of 150 participants per group; 300 participants in total.

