## Measures

### Primary outcome measures

#### Parental stress

*Perceived stress.* Perceived parental stress is measured using two self-report questionnaires: the Perceived Stress Scale (PSS-10, [41]) and the Postpartum Specific Anxiety Scale Research Short-Form (PSAS-RSF, [42]. The PSS-10 is a widely used instrument that measures the degree to which participants appraise situations as stressful and current levels of experienced stress. It consists of 10 items of a general nature. Example items are “How often have you been upset because of something that happened unexpectedly?” and “How often have you found that you could not cope with all the things that you had to do?”. For each item, participants are asked to indicate on a 5-point scale how often they felt or thought that certain way in the last month. Answer options range from 0 “never” to 4 “very often”. Total scores are calculated by reversing positively stated items and subsequently summing all items. A higher total score indicates a higher level of perceived stress. In addition to general perceived stress, maternal- and infant-focused concerns specific to the postpartum period are measured with the PSAS-RSF [42]. The PSAS-RSF is a shortened version of the PSAS, a validated 51-item instrument to measure postpartum anxiety [52]. The PSAS-RSF consists of 16 items and comprises four domains: (1) psychosocial adjustment to motherhood; (2) practical infant care anxieties; (3) maternal competence and attachment anxieties; and (4) infant safety and welfare anxieties. The measure demonstrated good construct validity and overall reliability [42]. Example items are “I have worried I will not know what to do when my baby cries” and “I have worried about my baby’s milk intake”. Participants are asked to rate each item with the answer that comes closest to how they have felt in the past 7 days, on a 4-point scale ranging from 1 “not at all” to 4 “almost always”. A total score and subscale scores can be calculated by summation of the individual item scores. Higher scores reflect higher levels of postpartum anxiety.

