#### Parental sensitive responsiveness

We operationalize the degree of parental sensitive responsiveness with three measures: the Non-Responsiveness Scale from the Maternal Responsiveness Questionnaire (MRQ, [45]), the Mother-to-Infant Bonding Scale (MIBS; [46]), and the Cry Perception Scale [47].

In the MRQ [45] seven contexts are presented, for example “When your baby is crying because he or she is sick or ill (e.g., has a cold, is teething, is feeling poorly after shots)” and “When your baby is crying even though he or she is well fed, well-rested, and has a fresh diaper”. For each context, different responses are described and participants are asked to rate how likely they are to respond in that specific way on a 5-point scale ranging from 1 “never” to 5 “always”. The full MRQ consists of three subscales (responsiveness, non-responsiveness, delayed responsiveness), with corresponding responses to the seven contexts. In this study, we only include the non-responsive scale with the corresponding responses: "You let your child cry for 10 min before you respond" and "You let your child cry until your child stops crying, no matter how long this takes". In combination with the seven contexts, the non-responsiveness scale consists of 13 items. Total scores of this subscale can vary between 13 and 65, with higher scores indicating less sensitive responsive behavior [45].

The MIBS [46] aims to measure feelings of parents towards their newborn babies. Parents are asked to indicate on four-point Likert scales ranging from "Very much" to "Not at all" to what extent each of the following eight feelings apply to them: “Loving, Irritated, Neutral, Happy, Dislike, Protective, Disappointed and Angry.” Total scores can vary between 0 and 24, with higher scores indicating more problematic feelings of the parent toward the infant and worse mother-to-infant bonding [46].

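### Three co-equal primary domains with nine measures are tested at p < 0.05 with no ranking or multiplicity control, while the sample size covers one comparison

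*Protocol article*

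**What the plan says.** The primary research question (Effects section) and Table 1 of the protocol article set out three primary domains without ranking them.

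- **Parental stress.** "Perceived parental stress is measured using two self-report questionnaires", the PSS-10 and the PSAS-RSF. Hair cortisol from one sample taken at T2 is added as the physiological measure.
- **Parental sensitive responsiveness.** "We operationalize the degree of parental sensitive responsiveness with three measures": MRQ non-responsiveness, MIBS and Cry Perception.
- **Child growth and development.** Weight SDS, length SDS and the D-score derived from the Van Wiechen items.

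Table 1 schedules all five questionnaires at T0, T1 and T2. The Statistical analysis section adds: "Differences between the intervention group and the control group at T1 and at T2 will be assessed", with correction for T0. The methods named there are t-tests and analyses of (co)variance, including multilevel and multivariate forms. The threshold is given in one sentence: "The level of significance (*p*-value) is set at *p* < 0.05 in all analyses".

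In the Sample size calculation section, "a medium effect size (Cohen’s *d* = 0.50) was included as the basis for the power and sample size calculation", and "84 participants per research arm are required for a power of 0.9". That number is then raised to 105 and 150 per arm for covariate adjustment or weighting and for non-response. Neither section mentions multiplicity.

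**The concern.** When nine measures share primary status, most of them are compared twice, and each test uses the same 5% threshold, 5% is no longer the error rate of the primary claim. The text fixes the threshold for every analysis, and it fixes no order of measures or time points that would limit the primary tests.

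The article plans to use the findings to update the intervention's registration (Dissemination) and hopes for a better effectiveness rating (Discussion). If one or two of many primary tests come out significant, the plan gives a reader no means of telling whether that is more than chance would produce. The stated power of 0.9 has the same limitation: it describes one test, not the primary family.

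**Working it through.** **1. Reproduce the sample size.** Inputs from the Sample size calculation section: d = 0.50, power 0.9, equal arms. Sidedness is not stated, so two-sided 0.05 is tried first.

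- n per arm = 2(1.960 + 1.282)² / 0.50² ≈ 84.1. Rounded up this is 85; the exact t-test gives 85.03. One-sided 0.05 would give 69.
- Power at n = 84 is 0.900 (normal) or 0.896 (t).
- 84 / 0.8 = 105 and 105 / 0.7 = 150, both exact.

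The plan's figures are therefore reproduced, within rounding, as one comparison at two-sided 0.05.

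**2. Count the primary tests.** Five questionnaires × 2 time points = 10. Adding cortisol, weight, length and D-score once each gives 14. One time point only would give 9.

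**3. Chance of at least one significant result with no effect, independent tests.**

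- Either direction: 1 − 0.95^14 = 51.2%; 1 − 0.95^9 = 37.0%.
- In favour of massage (0.025 per test): 1 − 0.975^14 = 29.8%; 1 − 0.975^9 = 20.4%.
- One multivariate test per domain, both time points together: 1 − 0.95³ = 14.3% in either direction.

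**4. Correlated tests.** The article gives no correlations, so these are assumptions. They were run by multivariate-normal simulation with 400,000 draws. The three values in each row are: the same measure at T1 and T2; different measures of one domain; stress against responsiveness questionnaires. Pairs of different questionnaires at different time points take the product with the first value. The growth and development measures correlate with each other at the second value. Cortisol with everything else, and growth with questionnaires, are set at 0.05.

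| Assumed correlations | 14 tests, either | 14 tests, favourable | 9 tests, either | 9 tests, favourable |
|---|---|---|---|---|
| 0.3 / 0.2 / 0.1 | 49.6% | 27.5% | 36.2% | 19.2% |
| 0.5 / 0.3 / 0.2 | 47.4% | 25.7% | 35.3% | 18.7% |
| 0.6 / 0.4 / 0.3 | 44.9% | 24.0% | 34.1% | 17.8% |
| 0.7 / 0.5 / 0.4 | 41.9% | 22.2% | 32.6% | 17.0% |
| 0.8 / 0.7 / 0.6 (extreme) | 35.3% | 18.5% | 28.6% | 14.9% |

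A common correlation across all 14 tests gives 44.0% and 22.6% at 0.3, and 34.9% and 17.5% at 0.5 (either direction and favourable).

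**5. Power once three tests are controlled.** The first Holm step uses 0.05 / 3 = 0.0167, with critical value 2.394. With 84 effective per arm, the expected test statistic is 0.50 × √(84/2) = 3.240. Normal power is Φ(3.240 − 2.394) = 0.80; the noncentral t gives 0.793. Keeping 0.90 would need 109 per arm before inflation, and 109 / 0.8 / 0.7 ≈ 195 recruited per arm against 150 planned.

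**The case against.** **A reader might put the chance of a falsely effective result at 40–50%.** The figures do not support that. The 40–50% includes significant results against massage; in its favour the rate is about half as large.

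**A reader might infer that any single significant test confirms the main hypothesis.** The article states no such rule. The hypothesis joins its components with 'and', so one could equally infer that all must succeed. On that reading the false-positive rate would be at most 5%, but the power statement would fail: with 0.90 per test and independence, three tests all succeed with probability 0.9³ = 0.73, and nine with 0.9⁹ = 0.39. The article states neither rule. The objection stands as a limit on the claim and is also a reason to write the rule down.

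**The count of 14 is one reading.** The mention of multivariate analyses could mean one test per domain, which lowers the rate to about 14%. However, the article does not make a multivariate test a gate before the single tests. Splitting Cry Perception into its three item groups would raise the count to 18, but the article counts it as one measure.

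**A multiplicity procedure may sit in an analysis plan that is not shown.** This is partly right. The article does not say that p-values are unadjusted, and Holm-adjusted values can be compared with 0.05. Absence alone would be no finding. Here, though, the article sets the threshold for every analysis, gives primary measures equal rank, and sizes the trial for one comparison. Those statements need reconciling wherever a procedure is kept.

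**The rating does not follow from one p-value.** According to the Background, an independent expert committee evaluates interventions and ratings depend on the amount of evidence. This objection stands and lowers the severity.

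**Conclusion.** The point holds as a should-fix. Three co-equal primary domains, nine measures and two time points for five of them are tested at p < 0.05 with no ranking or stated control, and the sample size rests on one comparison. If the 14 tests are run separately at two-sided 0.05 with no true effect, at least one significant primary result is expected about 40–50% of the time in either direction and about 20–30% of the time in favour of massage. For a single test the favourable rate would be 2.5%.

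These ranges assume independent to moderately correlated tests. Strong correlation brings them to about 35% and 18%, and multivariate testing by domain to about 14% in either direction. They also assume that each test keeps its own 5% level. Confounding in this non-randomized design could break that, and the Discussion acknowledges that residual confounding may remain.

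**What to change.** Before analysis, replace the blanket threshold sentence in the protocol and registry with the following:

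- **Confirmatory set.** One primary test per domain at one named time point. The investigators choose the measure, or they use one multivariate test per domain, which would keep hair cortisol in the stress domain.
- **Error control.** Holm across the three tests at an overall two-sided 0.05: the smallest p-value against 0.0167, the next against 0.025, the last against 0.05.
- **Success rule.** State what pattern across the three domains counts as support for the main hypothesis.
- **Everything else.** Report the remaining measures and the other time point as secondary, with confidence intervals.
- **Power.** At 84 effective per arm and d = 0.50, state about 0.79 for a univariate test at the first Holm step. A multivariate test would need its own calculation.

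The cost is lower stated power: the type II error at that step roughly doubles, from about 0.10 to 0.21. No extra data are needed if this is accepted; keeping 0.90 would take about 195 recruited per arm.

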## Dissemination

The results of the study will be shared with relevant stakeholders in a number of deliverables. The findings will be used to update the intervention registration in the Dutch intervention database [19] and will be summarized in two factsheets. The first factsheet will be focused on the results of the effectiveness study and the other will summarize the results of the process evaluation. These deliverables will be shared with the professional users of the intervention, PCH organizations, and with policy makers, in particular municipalities. Municipalities finance the PCH and are involved in the selection of interventions that are deployed. The factsheets will be distributed via networks of implementation partners, in newsletters and via relevant websites. Examples include the national center for PCH (in Dutch: Nederlands Centrum Jeugdgezondheid) and training centers for infant massage teachers. Study results will also be translated into a practical Individual Shantala Infant Massage brochure for parents, to inform our study participants and to be used by PCH professionals to inform parents about the intervention. Relevant findings will also be published on relevant websites for parents, available for the general public. Finally, results will be shared with fellow researchers at relevant (inter)national symposia and conferences and through publications in national and international scientific journals.

## Discussion

Dutch PCH professionals have the opportunity to support vulnerable families in early life, since they are in regular contact with most parents of young children. However, there is a lack of available, easily accessible evidence-based interventions for this target group [20]. The preventive, short-term, accessible intervention Individual Shantala Infant massage, could be a promising answer to this demand.

This study protocol presents the design of a non-randomized trial to evaluate the effects and the intervention process of Individual Shantala Infant Massage in the daily practice of PCH. It is hypothesized that the intervention will lead to an increase in parental sensitive responsiveness, lower reported and physiological stress of the parent and improved child growth and development in the intervention group, compared to a control group where the intervention is not part of the standard PCH care offer. Secondary hypotheses are that the intervention will lead to increased parenting confidence and a decrease of parental concerns (e.g. about crying, feeding and sleeping behavior of the infant). An exploratory secondary research question is whether specific subgroups profit more or less from this intervention. The intervention process is evaluated based on logbooks of professionals, questionnaires for parents and interviews.

This study has several strengths. First, it is conducted in the daily practice of the PCH, which enables us to investigate the intervention in ‘real life’ rather than in an experimental setting, which supports the generalizability of our findings. Second, the study has a mixed-method design, combining information from multiple sources, including questionnaires, a physiological measurement of parental stress, PCH data on child growth and development, and an evaluation questionnaire, logbooks of the intervention sessions and interviews with both parents and professionals. However, the study also has limitations that need to be noted. The study is non-randomized, which may affect the comparability of the groups. In order to reduce the potential effects of non-randomization, we use a pre-post design. Furthermore, we attempt to control for possible group differences by assessing the most important confounders. However, the possibility of residual confounding remains and should be taken into account when interpreting the results. We also expect to encounter some challenges. The target group of the intervention, and thereby of this study, consists of parents with a young baby who may be vulnerable. This is a group where inclusion may be difficult and drop-out is to be expected. We hope to overcome this challenge by recruiting participants through and in close collaboration with PCH professionals who already are in direct contact with these parents. Furthermore, we try to lower the threshold to participate by making the study information accessible and comprehensible, by minimizing the burden by selecting questionnaires that are as short and as simple as possible, and by maintaining low-key contact with participants.

This is the first controlled effect and process evaluation of the intervention Individual Shantala Infant Massage. The study can contribute to the evidence base of individual infant massage as applied in Dutch preventive child healthcare practice. As a result, the intervention may be acknowledged at a higher level of effectiveness in the national intervention database. Study results can inform parents, PCH professionals, researchers, and policy makers, both inside and outside the Netherlands, on the feasibility and effectiveness of the Individual Shantala Infant Massage intervention. A strengthened evidence base and insights on implementation and required conditions can help to facilitate a broader implementation of this intervention by other PCH organizations in the future. This contributes to easily accessible support for vulnerable families in order to reduce (effects) of stress and to improve positive parenting and parent-infant relationships.

